# Nitrate-rich beet juice intake on cardiovascular performance in response to exercise in postmenopausal women with arterial hypertension: study protocol for a randomized controlled trial

**DOI:** 10.1186/s13063-023-07117-2

**Published:** 2023-02-07

**Keywords:** *Beta vulgaris*, Nitrate, Hypertension, Post-menopause, Cardiovascular physiological phenomena, Sports nutritional sciences

## Abstract

**Background:**

There is no evidence of the use of beetroot juice with a previously recommended dose of nitrate (NO3) (> 300 mg) on the cardiovascular performance during and recovery following exercise in postmenopausal women with systemic arterial hypertension (SAH).

**Methods:**

We will investigate the effects of beetroot juice rich in NO3 acutely (800 mg) and during a week with daily doses (400 mg) on blood pressure, heart rate (HR), cardiac autonomic control, endothelial function, inflammatory, hormonal, and stress biomarkers oxidative stress and enzymes involved in nitric oxide synthesis and mitochondrial regulation, under resting conditions, as well as mediated by submaximal aerobic exercise sessions. Through a randomized, crossover, triple-blind, placebo-controlled clinical trial, 25 physically inactive women with SAH will undergo an acute and 1-week trial, each with two intervention protocols: (1) placebo and (2) beetroot, in which will ingest beet juice with or without NO3 in its composition with a 7-day washout interval. On collection days, exercise will be performed on a treadmill for 40 min at a speed corresponding to 65–70% of VO2peak. The collection of variables (cardiovascular, autonomic, and blood samples for molecular analyses) of the study will take place at rest (135 min after ingestion of the intervention), during exercise (40 min), and in the effort recovery stage (during 60 min) based on previously validated protocols. The collections were arranged so that the measurement of one variable does not interfere with the other and that they have adequate intervals between them.

**Discussion:**

The results of this research may help in the real understanding of the nutritional compounds capable of generating safety to the cardiovascular system during physical exercise, especially for women who are aging and who have cardiovascular limitations (e.g., arterial hypertension) to perform physical exercise. Therefore, our results will be able to help specific nutritional recommendations to optimize cardiovascular health.

**Trial registration:**

ClinicalTrials.gov NCT05384340. Registered on May 20, 2022.

## Introduction

### Background and rationale

Physiological changes in the non-reproductive phase of women impose a high risk for the development of systemic arterial hypertension (SAH), given that the abrupt drop in estrogen levels reduces the production of endothelial relaxing factors, such as nitric oxide (NO) [1]. To the detriment of this, the prevalence of SAH in postmenopausal women tends to increase compared to men of the same age. Consequently, females become more prone to cardiovascular and cerebrovascular diseases [2].

Although there has been a great advance in managing the treatment of SAH, the disease control rates in Brazil are still considered unsatisfactory [3]. A recent meta-analysis with national data revealed a variation between 43.7 and 67.5% of SAH control rates in primary care [4]. Therefore, therapeutic adjuvants are necessary for optimizing cardiovascular functioning in SAH, among which beetroot juice has been gaining notoriety.

Betaine and nitrate have better-established purposes among the various nutritional compounds present in beets. Betaine is a potent anti-inflammatory and antioxidant compound [5], in addition to having an essential role in eliminating toxic metabolites from the body (e.g., homocysteine) [6] and reducing the risk of a heart attack myocardial infarction [7].

Nitrate (NO3), when ingested, is partially reduced to nitrite (NO2) by oral bacteria from NO3 reductase. Subsequently, upon reaching the stomach, NO2 reacts with low pH and is transformed into NO, which is easily transported across cell membranes into the bloodstream, where it plays a crucial role in vasodilation. The NO2 remaining in the stomach is absorbed in the initial parts of the duodenum and follows other pathways to increase NO production in the circulation [8]. In addition to the previously described exogenous pathway, NO can also be synthesized endogenously via the l-arginine + O2 pathway, mediated by NO-synthase enzymes [9]. Recent meta-analyses of clinical trials have shown that NO3 consumed through beetroot juice lowers blood pressure more clearly [10, 11] than in its salt form (e.g., sodium/potassium NO3) [12]. There are assumptions that this occurs through the interaction between NO3 and the vitamins, minerals, and phenolic compounds present in beet juice, generating more intense pressure and vascular responses [10].

Considering that the endogenous production of NO is reduced with aging [13], it was recently confirmed that the hypotensive effects caused by beetroot juice are more evident in older adults (50 to 70 years of age) when compared to a young population (18 to 30 years of age) [14]. In addition, a meta-analysis recently published by our group showed that in patients with SAH, NO3-rich beetroot juice supplementation was able to reduce systolic blood pressure by − 4.95 mmHg (95% CI: − 8.88; − 1.01) without significant differences to diastolic blood pressure [10].

Accordingly, physical exercise is considered one of the non-drug therapeutic strategies that directly helps to reduce blood pressure levels by causing post-exercise hypotension (PEH) [15] and contributing to increased baroreflex sensitivity [16]. HPE has excellent clinical value for hypertensive patients, as it can be used as a strategy to reduce blood pressure levels both acutely and chronically. Aerobic exercise is considered one of the most efficient to generate PEH [17–19].

In conjunction with heart rate (HR) and blood pressure (BP) levels, heart rate variability (HRV) has been used as a non-invasive and independent metric for assessing cardiovascular risk [11, 20, 21]. Through the adjacent intervals between consecutive heartbeats (RRi), it is possible to analyze the behavior of autonomic efferents (parasympathetic and sympathetic) on the heart [22, 23]. Part of the effects caused by hypertension on cardiac activity involves adjustments in the autonomic nervous system (ANS), and therefore, in hypertensive patients, there is a decrease in HRV at rest [24], and after exercise, there is a delay in recovery of parasympathetic modulation [25]. These two factors are evidence of autonomic dysfunction and cardiovascular inadaptability that certainly contribute to the emergence of disorders and adverse cardiovascular events [26] and a risk factor for overall mortality [27]. In SAH, endothelial dysfunction is documented in the macro- and microcirculation of the coronary, peripheral, and renal circulation. These effects are mainly caused by decreased endogenous nitric oxide production through increased oxidative stress and endothelial damage caused by increased blood shear force [28].

To date, studies that have investigated the effects of NO3-rich beet juice on the cardiovascular exercise responses of hypertensive patients applied it in an acute dosage of 35 mL and, therefore, with a limited amount of NO3 (200 mg) [29, 30]. But these dosages are at odds with the pharmacodynamic and dose-response studies of beet juice rich in nitrate, and this may be the main factor why there are no summative effects on the hypotensive response [29] and autonomic recovery [30] after exercise were found in women with arterial hypertension. It has already been shown that only after 4 to 6 days of beet juice ingestion (> 300 mg of nitrate) the bioavailability of inorganic NO3 is increased to cause physiological effects [31]. Furthermore, the study by Wylie et al. [32] determines that an optimal acute dosage of beetroot juice for cardiovascular outcomes is 140 mL, that is, approximately 800 mg of nitrate. Our study aims to resolve these issues by applying the dosages recommended by the studies by Wylie et al. [32] and Bailey et al. [31].

### Objectives and hypotheses

The objective is to investigate the effects of beetroot juice rich in NO3 acutely (800 mg) and for a week with daily doses (400 mg) on blood pressure; heart rate; cardiac autonomic control; endothelial function; inflammatory, hormonal, and oxidative stress biomarkers; and enzymes involved in nitric oxide synthesis and mitochondrial regulation, under resting conditions, as well as mediated by submaximal aerobic exercise sessions.

We hypothesize that interventions with NO3 from the BRJ, both acutely and during a 1-week intervention, will improve cardiovascular parameters in response to exercise and in the recovery from the submaximal exercise test.

### Trial design

The study is classified as a randomized, crossover, triple-blind, placebo-controlled clinical trial and will have two arms. The study protocol is registered on the ClinicalTrials.gov platform (NCT05384340) and described according to the Standard Protocol Items: Recommendations for Interventional Trials (SPIRIT) checklist. The results from this clinical trial will be described following the Consolidated Standards of Reporting Trials (CONSORT) guidelines.

## Methods: participants, interventions, and outcomes

### Study setting

The study will be conducted at the Laboratory of Exercise Physiology and Metabolism (LAFEM) of the School of Physical Education and Sport of Ribeirão Preto, University of São Paulo (EEFERP-USP).

Participants will visit the laboratory seven times for the familiarization, collection, and measurement of variables. Sessions will be held between 7:30 am and 11:00 am to standardize the influence of the circadian rhythm on the parameters evaluated. The environment will be controlled with temperature between 22 and 25 °C and humidity between 60 and 70%.

On collection days, 2 h before data measurement, participants already in the laboratory will ingest beetroot juice (Beet It, James White Drinks, Ltd.) with or without nitrate in its composition. The juices will be identical in their organoleptic characteristics, and therefore, only the amount of nitrate will differ between them.

### Eligibility criteria

Women aged between 50 and 70 years living in the city of Ribeirão Preto, São Paulo, Brazil, with a previous diagnosis of SAH [3], will be recruited. Study participants must be physically inactive according to the Modified Baecke Questionnaire for the elderly (QBMI) [33]. We will consider the systolic blood pressure values between 120 and 159 mmHg or diastolic blood pressure values between 80 and 99 mmHg [34]. To be eligible to participate in the study, participants must have a diagnosis of post-menopause (amenorrhea for a period equal to or greater than 12 months) [35], have health conditions to practice physical activity according to the Physical Activity Readiness Questionnaire (PAR-Q), and not having a history of previous acute myocardial infarction or stroke confirmed by medical history, in addition to having no known allergy and/or intolerance(s) to nitrate, milk, and gluten. Those that interfere with the pH of the stomach (e.g., proton pump inhibitors) and/or using drugs that directly affect cardiac autonomic control (e.g., beta-blockers and calcium channel antagonists) will be excluded from the study. The other medications used by the participants will be recorded to be included as adjustment variables in the statistical analysis.

### Interventions

#### Intervention description

The purpose of the study is to identify the effects of NO3 from beetroot juice, and therefore, the study was divided into two arms: (a) beetroot juice rich in nitrate and (b) beet juice without nitrate. The other protocols will be applied to the participants at the exact times and times of the day. In addition, because it is a crossover study, all participants will undergo all interventions equally.

Each protocol will last for 7 days, and its order of execution will be established through a randomization process. As this is a crossover study, each participant will participate in both protocols. Between one protocol and another, a 7-day washout interval will be given for the purification of the compounds provided by the protocols. Subsequently, the intervention contrary to the first will be provided, with the dynamics of the intervention being the same for both phases. Participants will receive eight units of juice bottles corresponding to the first intervention (placebo or nitrate) on the first laboratory visit. On the first day of intervention of each protocol, they will take two units (140 mL–800 mg of NO3), and from the second to the seventh day, they will take one unit (70 mL–400 mg of NO3) per day. Of the eight units (100%), six bottles (75%) will be destined for the participants to take home. On the seventh day of the intervention, the participants will take the last unit of juice at home and return to the laboratory for the last evaluation.

On the days that they do not visit the laboratory and on the last day of evaluation, the participants will drink the juice in the morning and on an empty stomach before brushing their teeth. After drinking the juice, we will ask them to take a 30-min break to consume breakfast. Photographs or videos of the participants ingesting the juice will be requested daily and sent to the researcher.

Participants will not be informed about the order of administration of interventions. The researcher responsible for collecting and measuring the variables studied will also be blinded so as not to know which protocol will be administered. An independent researcher will be responsible for taking the juice and delivering it to the responsible researcher. In addition, another independent researcher/collaborator will be responsible for the statistical analysis of the data, so that he will be blinded so that he is not aware of which protocol order will be analyzed. Based on the steps previously described, the design of a randomized, triple-blind, placebo-controlled trial will be achieved. The quality of blinding will be assessed at the end of the study by asking each participant which beverage they believe they are ingesting in each of the two protocols.

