
#### Exercise variables

On the first day, the collections will occur after the participants ingested 140 mL of beet juice (with or without nitrate). The seventh day of beet juice ingestion (70 mL) (with or without nitrate) will also be collected. On the collection days (first and seventh days of intervention), the variables will be obtained at the following times (Fig. 1):

I)Rest phase (zero to 135th min): After drinking the juice, the participants will remain at an initial rest in a sitting position. Then, 30 min before starting the measurements, the participants will be instructed to empty their bladders. Upon returning to the room, a recording strap (Polar® H10) will be placed on the chest, in the region of the distal third of the sternum, to record beat-to-beat HR throughout the collection, mediated by a heart rate monitor (Polar® RS800CX, Finland). Then, the participants will be placed on a stretcher in the supine position and will remain at rest. After the remaining time, HR values will be recorded (120th minute), HRV recording (120th to 125th min), systolic blood pressure (SBP) (125th minute), diastolic blood pressure (DBP) (125th minute), blood collection (15mL) (125th min), and analysis of endothelial function (flow-mediated dilation) (125th to 135th min).II)Physical exercise (135th to 175th min): Participants will perform the physical exercise for 40 min on a treadmill at a speed corresponding to 65–70% of VO2peak [29]. In this phase, the highest HR value reached during the exercise will be recorded, and the HRV recording will also be carried out in the last 5 min (35th–40th min).III)Recovery phase (175th to 235th min): At the end of the activity, the participants will be placed in the supine position again and will be monitored for another 60 min, recording their HR at 30 s, 60 s, 120 s, 180 s, and 300 s. Blood collection (15 mL) will be performed between 5 and 10 min after exercise. HRV will be recorded after exercise at the following times: 0–5 min, 10–15 min, 20–25 min, 30–35 min, and 40–45 min. SBP and DBP will be recorded after exercise at the 45th minute and 60th minute post-exercise. To avoid errors in the measurements of the evaluated parameters, a single evaluator will perform these measurements throughout the experiment. The flow-mediated dilation technique to assess endothelial function will be employed after exercise during the 50th–60th minute post-exercise interval.

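### Day 7 has conflicting rules for where the juice is drunk and what is eaten, and no rule carries a home intake time to the laboratory clock

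*Protocol article*

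**What the plan says.** Four sections of the protocol article bear on day 7.

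- **Study setting:** "On collection days, 2 h before data measurement, participants already in the laboratory will ingest beetroot juice". No day is exempted.
- **Exercise variables:** "On the collection days (first and seventh days of intervention), the variables will be obtained at the following times". One schedule serves both days and runs from the drink: "Rest phase (zero to 135th min): After drinking the juice, the participants will remain at an initial rest in a sitting position". Resting blood pressure is at minute 125, exercise runs from minute 135 to 175, and blood pressure is repeated 45 and 60 minutes after exercise. This section names no place of intake.
- **Intervention description:** on day 7, "the participants will take the last unit of juice at home and return to the laboratory for the last evaluation". The fasting-morning routine used on days without a visit is extended to the last evaluation day, and a 30-minute break tied to breakfast follows the drink. On supply: "Of the eight units (100%), six bottles (75%) will be destined for the participants to take home". Daily photographs or videos of the intake are requested.
- **Relevant concomitant care:** on laboratory-visit days there is no breakfast, and 40 g of whey protein is the standard meal before the experimental procedures.

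**The concern.** Day 7 is the only occasion on which the 1-week hypothesis is tested, and blood pressure is the primary outcome. Staff following Study setting would seat a woman in the laboratory, watch her drink and start the clock. Staff following Intervention description would receive a woman who had already drunk the juice, possibly eaten breakfast, and travelled. Resting blood pressure, nitrite, heart rate variability and flow-mediated dilation would then be measured after different preparation and, unless the home intake time is known, at an uncertain interval from the dose. In a small crossover such variation goes into the within-woman error on which precision depends. It also mixes any day-1 to day-7 difference with differences in setting, meal and timing.

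**Working it through.** No power or sample-size formula applies. The check is a count, a timeline and a comparison of the sections.

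**1. Bottle count (Intervention description).** Units per period = 2 (day 1) + 6 × 1 (days 2 to 7) = 8. After the two day-1 units, 8 − 2 = 6 remain, and 6/8 = 75%. This reproduces the stated figure and matches home intake on all of days 2 to 7. Had the day-7 unit been kept in the laboratory, 5/8 = 62.5% would go home. The home-intake sentence is therefore not a slip of wording.

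**2. Timeline (Exercise variables).** From ingestion: 135 min rest + 40 min exercise + 60 min recovery = 235 min. Post-exercise blood pressure falls at 175 + 45 = 220 and 175 + 60 = 235 min. Study setting's 2 h equals the 120th minute, when measurements begin, so the two sections agree on the nominal interval.

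**3. What can and cannot be kept if intake is at home.** Bladder emptying, strap placement and supine rest start 30 min before measurement, at minute 120 − 30 = 90. A woman who arrives within about 90 min of drinking can still complete them. The seated rest starting straight after the drink cannot be kept while she travels.

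**4. Rules for day 7 side by side.**

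| Item | One rule | Other rule |
|---|---|---|
| Place of intake | Laboratory (Study setting, with Exercise variables defining day 7 as a collection day) | Home (Intervention description) |
| Food | No breakfast, 40 g whey (Relevant concomitant care) | Juice linked to breakfast (Intervention description) |
| First part of rest | Seated from ingestion (Exercise variables) | Travel, if intake is at home |
| Minute 0 | Ingestion (Exercise variables) | No competing rule, but no stated way to bring a home intake time to the laboratory clock |

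**5. Session window (Study setting).** 7:30 to 11:00 is 210 min, and 235 − 210 = 25. Laboratory intake at 7:30 would end the session at 11:25; ending by 11:00 needs intake by 7:05. The same arithmetic applies on day 1, so it does not settle the day-7 question. It is one more timing statement to align.

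**6. Extent.** Two periods × two collection days = 4 sessions per woman, of which 2 are day-7 sessions. With three blood pressure time points per session, 2 × 3 = 6 of 12 are affected. For the sixteen women in Sample size, that is 32 of 64 sessions.

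**The case against.** The strongest reply is that timing is anchored: Exercise variables counts from the drink, and Study setting gives the same 2 h. If a woman drinks at home and staff count from that moment, the interval is unchanged. Home intake is also documented by the requested photographs or videos. Intervention description says that procedures take place at the same times and in the same way in both phases, so any imprecision falls on nitrate and placebo alike. Randomisation, the comparator and the day-1 comparison are untouched.

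Most of this stands, and it rules out three stronger readings that a reader might infer:

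- **That time zero is undefined, or that the laboratory clock restarts on arrival.** The document states neither.
- **That part of the planned 5 mmHg effect is lost.** This would need a clock restart, a travel time, a time of peak effect and a rate of fading, none of which is given. Day 7 also follows repeated dosing, and Sample size ties the 5 mmHg to no minute after a dose.
- **That the treatment comparison is biased.** Both treatments follow the same procedure.

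The conflict itself is not answered. The protocol does not exempt day 7 from the laboratory rule, reconcile breakfast with the whey meal, or say that the time of a home drink is recorded and used as minute 0. A requested photograph is not a recorded time.

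**Conclusion.** The point holds as a contradiction in the current text. On day 7 the place of intake and the pre-test meal are each governed by two rules that cannot both be followed, and the early seated rest is lost if intake is at home. It affects half of the collection sessions and all the data for the 1-week hypothesis, including the primary outcome.

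The likely consequence is added variability in the intake-to-measurement interval and poorer comparability of day 1 with day 7, more than bias between nitrate and placebo. Its size cannot be stated in mmHg from this document. The conclusion rests on reading the collection-day rule as covering day 7, which the definition in Exercise variables supports, and on the routine for the last evaluation day including the breakfast sentence that follows it.

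**What to change.** 1. Reconcile Study setting, Intervention description, Relevant concomitant care and Exercise variables so that one place of intake, one meal rule and one time zero apply on day 7 in both periods. Which rule is kept is for the investigators to decide. Check the session window against the 235-min schedule at the same time.
2. Record the clock time of intake at every collection session, wherever it takes place, and count all stated minutes from it.
3. For sessions already run, state which procedure was followed. Where intake times exist (for example, from photograph or video timestamps), report the intake-to-blood-pressure interval by treatment and the number of sessions without a time. Repeat the day-7 mixed-model analysis with the interval as a session-level covariate, labelled as a sensitivity analysis.

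The cost is wording in four sections, one time field on the collection form, one short table and one sensitivity analysis, with the change passing through the ethics committee and registry update that the protocol already describes. The retrospective part is possible only where intake times were kept.
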